### Secondary Outcome Measures

The secondary outcome measures will report on the physiological factors (short-term effects) illustrating underlying mechanisms of early intervention undertaken in the study. Blood samples (8 ml) will be obtained from the patients' arterial line, for the analysis of cytokines, blood lactate and mtDNA levels pre and post intervention during the trial. All blood samples taken will be centrifuged (Spintron GT-25E/LL, Australia) for 15 minutes at 3000 rpm, within 20 minutes of collection. Plasma from the whole blood for the cytokine analysis and peripheral blood mononuclear cells (PBMC) forming the buffy coat pellet for DNA isolation will be stored at -80°C.

#### Inflammatory Biomarkers

Biomarkers will be measured before intervention and 30 minutes post intervention daily (week 1) and thereafter twice weekly (till ICU discharge). The acute inflammatory response of early exercise in sepsis will be measured by changes in levels of pro-inflammatory cytokines (IL-6 and TNF-α) and anti-inflammatory cytokine (IL-10). IL-6, IL-10 and TNF-α will be measured from plasma samples with the Milliplex cytokine panels from Millipore (Billerica, MA, USA) using a Luminex 100 assay, with inter and intra-assay CV < 7%.

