### Early Rehabilitation may Modulate Detrimental Effects of Sepsis

The roles of pro-inflammatory cytokines, mitochondrial changes and muscle proteolysis in causing sepsis-induced myopathy in critically ill patients are hypothesised from animal models [6,14]. It is postulated that exercise can modulate cytokine levels [47], ROS production [50] and ATP levels [49] in patients with sepsis. In conjunction with an early mobility protocol, ambulation during mechanical ventilation in the early stages of critical illness is becoming widely practiced [50-52], especially with interruption of sedation [53-55]. Conservatively, simple passive movements [56] and neuromuscular electrical stimulation [45] as a precursor to active mobilisation can induce microcirculatory changes that may attenuate the anti-inflammatory effects in early sepsis.

Overall, early rehabilitation in critical illness seems to show reduced time on the ventilator, improved quality of life and reduced hospital and ICU stay [7] but this is not specific to sepsis. Furthermore, the short-term systemic effects of exercise for ICU patients remain highly speculative and debatable. The impact of exercise in the early stages of critical illness on effects such as oxidative stress and microcirculatory alterations have been unexplored and speculated from other populations. Exploring these physiological factors in response to exercise can contribute to determining the safety of early rehabilitation in sepsis.

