### Data Management and Statistical Analysis

A baseline comparison using both student t-tests and chi-square for equal proportions of demographic data will be done between groups at enrolment. Data will be analyzed using SPSS Version 17.0. The distribution, range of scores and heterogeneity will be examined for participants in both groups. Mean changes scores, standard deviations and 95% confidence intervals will be calculated and specific analysis detailed under each outcome measure will be performed. Repeated measures, between/within analysis of variance (ANOVA) will be performed to investigate for the main effects of time and group. Post hoc analyses will then be performed to ascertain where the differences occur. A Bonferroni correction will be used as the post hoc measure as there are multiple outcome measures. Analysis will be by both intention-to-treat and per-protocol method. Any violations of the protocol will be noted. Statistical significance will be set at p < 0.05 and p < 0.025(two-tailed). All efforts will be taken to avoid missing data but if it occurs a carry forward imputation will be done and linear mixed modelling will be used for overall analysis. Reasons for loss of follow up will be recorded.

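### Cytokine sampling ends at ICU discharge, so the planned ANOVA group effect with carry-forward can depend on length of stay

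*Protocol article*

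**What the plan says.** Under Inflammatory Biomarkers, the cytokine sampling schedule reads: "Biomarkers will be measured before intervention and 30 minutes post intervention daily (week 1) and thereafter twice weekly (till ICU discharge". No last day common to all patients is set. The stated target is acute: "The acute inflammatory response of early exercise in sepsis will be measured by changes in levels of pro-inflammatory cytokines (IL-6 and TNF-α", with IL-10 as the anti-inflammatory marker.

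Under Data Management and Statistical Analysis, one plan serves all repeated outcomes: "Repeated measures, between/within analysis of variance (ANOVA) will be performed to investigate for the main effects of time and group". On missing data it says that "if it occurs a carry forward imputation will be done and linear mixed modelling will be used for overall analysis". It adds that "specific analysis detailed under each outcome measure will be performed", but the cytokine section gives no analysis beyond changes in levels. Neither section says how occasions after discharge or death are treated.

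**The concern.** Classical repeated-measures ANOVA needs the same occasions in every patient. Here the series ends when the patient leaves ICU, so the late cells must be filled or the patient dropped. If they are filled by carry-forward, a patient who leaves early has an early value copied into all later occasions. The main effect of group averages over occasions. When levels drift over days, that average depends on how long each arm stayed as well as on treatment.

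Stay could plausibly differ by arm. In general ICU patients, the protocol says, "early rehabilitation in critical illness seems to show reduced time on the ventilator, improved quality of life and reduced hospital and ICU stay".

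The Background wants assurance that exercise does not worsen inflammation, and Hypotheses and Aims predicts lower pro-inflammatory and higher anti-inflammatory cytokines. If levels fall over time, the arm that leaves sooner shows higher averages. For IL-6 or TNF-α this could pass for harm, and for IL-10 for the predicted benefit. If levels rise over time the direction reverses; if they are flat there is no artefact.

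**Working it through.** The protocol states no figure on this point: no cytokine sample size, rate of change or expected ICU stay. There is nothing to reproduce, and the size below rests on assumptions.

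**Inputs**
- From the protocol: daily sampling in week 1, then twice weekly to ICU discharge; 126 patients per arm (Sample size).
- Assumed: log cytokine level falls 0.08 per day (range 0.05 to 0.15); median stays of 9 v 12 or 7 v 12 days; no treatment effect on any day.

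**Step 1: series length.** For a stay of L days (L at least 7), sampled days = 7 + 2(L − 7)/7. This gives 7 for a 7-day stay, 9 for 14 days, 11 for 21 days and 13 for 28 days.

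**Step 2: hand check of carry-forward.** Take 13 occasions on days 1 to 7, 10, 14, 17, 21, 24 and 28, with every patient's last value carried to the end.
- Stay of 9 days: last sample on day 7. Mean day represented = (28 + 6 × 7)/13 = 70/13 = 5.38.
- Stay of 12 days: last sample on day 10. Mean day represented = (28 + 10 + 5 × 10)/13 = 88/13 = 6.77.
- Difference = 18/13 = 1.38 days. At 0.08 per day this is 0.11 log units. At 0.05 to 0.15 per day it is 0.07 to 0.21.

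A fixed 7-day stay gives the same result as 9 days, because no sample falls between days 7 and 10. Variation in stay separates the two cases.

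**Step 3: simulation with varying stays.** 126 per arm, log-normal stays (log SD 0.5), between-patient SD 0.7, residual SD 0.5, decline 0.08 per day, no treatment effect. There were 150 runs, with the mixed model fitted in 25 of them. Entries are the mean group difference in log units, shorter-stay arm minus the other.

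| Median stay, days | Mean of available samples | Mean after carry-forward | Mixed model, day as factor |
|---|---|---|---|
| 12 v 12 | 0.02 | 0.02 | 0.05 |
| 9 v 12 | 0.09 | 0.10 | 0.02 |
| 7 v 12 | 0.13 | 0.15 | 0.00 |

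Monte Carlo error is about 0.008 for the first two columns. In the first row the true value is zero by construction, so 0.02 and 0.05 there are noise. The mixed-model column is imprecise and only suggestive. The firmer argument is structural: with day in the model, arms are compared on the same day, so a difference in stay does not by itself enter the group contrast when discharge is unrelated to unobserved levels.

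Back-transformed, 0.10 and 0.15 log units are e^0.10 = 1.11 and e^0.15 = 1.16, that is, levels 11% to 16% higher with no treatment effect.

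**Step 4: within-session change.** With a 30-minute session and a sample 30 minutes later, the pair is about 1 hour apart. The assumed drift over that time is 0.08/24 = 0.003 log units. The slow decline all but cancels.

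**The case against.** The strongest reply is that the analysis text is generic. It names no cytokine occasions or window and defers to outcome-specific analyses, and a condensed article may leave windows and time coding to a fuller document. It also names a linear mixed model and post hoc analyses to locate differences. All of this stands. A reader might infer that the group effect is tested across every occasion; the protocol does not say so. What remains is that ANOVA main effects and carry-forward are positively named, and that carry-forward is coupled with the mixed model instead of being replaced by it.

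A reader might also infer that the schedule itself is faulty because week 1 is over-represented: 7 of 9 sampled days (78%) in a 14-day stay, against 50% of the days. The protocol does not support that. Dense early sampling fits an aim of measuring the acute response. The imbalance affects only an effect averaged over occasions, not day-specific or group-by-day contrasts.

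A third tempting reading is that the protocol expects its intervention to shorten ICU stay. The statement on stay summarises work in general ICU patients; the same sentence adds that it is not specific to sepsis, and shorter stay is not among the trial's hypotheses. Unequal stays are a possibility to guard against, not a stated expectation.

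Finally, if the comparison is of within-session changes, Step 4 shows that the problem is very small unless the acute response itself drifts over days.

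**Conclusion.** The point holds for between-arm comparisons of cytokine levels across days. With sampling ended by discharge, ANOVA main effects and carry-forward let the group effect depend on length of stay. Under the assumed decline and stays the artefact is about 0.10 to 0.15 log units. It requires three things: levels that change over days, stays that differ between arms, and carry-forward applied to occasions after discharge. The protocol supplies no value for the first two and leaves the third open.

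The outcome is secondary and mechanistic and the primary outcomes are untouched, so severity is low to moderate.

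**What to change.** For the between-arm cytokine comparison, replace ANOVA main effects with the linear mixed model already named: log values, with day since randomisation, group and group-by-day, adjusted for the baseline value. State that nothing is carried forward past ICU discharge or death. Report the group contrast by day. Make days 1 to 7, where sampling is daily, the main contrast, and report later days from the same model as supportive. Keeping the later days matters, because a week-1-only analysis would miss any effect that appears afterwards.

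The cost is analysis wording only; sampling does not change. Later samples carry less weight in the main cytokine test. Patients discharged or dead before day 7 still stop contributing, and the model does not correct for discharge or death that depends on unobserved cytokine levels. That should be stated as a limitation.

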#### Muscle Mass

Fat free mass will account for muscle mass (lean tissue) measured at baseline (week 0) and weekly thereafter (till ICU discharge) using the Multi-Frequency Bioelectrical Impedance Spectroscopy (BIS) Machine (ImpediMed SFB7, ImpediMed Ltd, Brisbane, Australia). Measurements will be taken at a standardised time of the day as practicable for validity [67] and at standardised anatomical landmarks for reproducibility of results [68]. Pairs of gel electrodes will be placed on the hand and foot on the right side of the body with the participant positioned in supine. ICU monitoring will continue during measurement without interference [69]. An estimate will be made of the critically ill patients' fluid balance. Urinary catheters will be emptied, prior to measurement. If subjects are known to have ascites, a pleural effusion or a renal replacement therapy, measurements will not be done. Percentage fat free mass will be measured in triplicate and analysed to reflect if proteolysis had occurred and resulted in the loss of muscle mass [70].

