## Background

Critical Illness and trauma are the primary sources of intensive care unit admissions. An estimated 2-11% of these patients require prolonged stays in the ICU which accounts for 25-45% of total ICU days [1]. Survivors of intensive care, especially those with prolonged admissions, may exhibit severe psychological and physical problems [2] and have a lower health-related quality of life up to one year following discharge from the hospital [3]. Almost a quarter of these patients are either admitted with or develop sepsis i.e. a severe, specific inflammatory response to infection, during the course of their stay in the ICU with major immediate and long-term effects on morbidity and mortality [4]. Patients with sepsis can have a worse outcome both in terms of overall functioning and mortality rates [5]. There is evidence that specific decreases in muscle mass and muscle force occur in sepsis syndromes caused by a variety of mechanisms [6]. This has major effects on the health and productivity of survivors as well as ultimately impact on the availability of ICU and hospital beds, surgical waiting lists, health costs and society.

Hypothesising that light to moderate exercise can partially reverse this condition without causing harm to critically ill patients, several exercise trials conducted in general intensive care patients have indicated positive findings that early intervention with exercise is able to prevent critical illness weakness syndromes, loss of muscle mass, decrease duration of mechanical ventilation, length of hospital and ICU stay and improve overall quality of life [7]. Specifically however, it is important to investigate early rehabilitation in patients with sepsis syndromes as the inflammatory process in sepsis can aggravate and accelerate the rate of muscle wasting in addition to the immobility associated with the disease in its early stages. It is equally important to ensure that early exercise in sepsis does not result in oxidative stress or cause substantial tissue injury potentially worsening the inflammatory reaction. The physiological reasons for improvement or adverse effects require investigation (Figure 1).

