#### Oxidative Stress Markers

Oxidative stress will be determined through changes in mitochondrial DNA levels. Mitochondrial DNA copy number in the PBMC will be measured by determining relative amounts of mitochondrial to nuclear DNA using quantitative real-time PCR. Mitochondrial DNA (mtDNA) levels in the peripheral blood will be measured at baseline (week 0) and weekly thereafter (till ICU discharge). Total DNA from the blood sample will be extracted from the buffycoat using a DNA Analysis Kit (Machery Nagel Blood XL, Germany) and mtDNA quantity will be analysed using SYBR Green Master Mix Real Time PCR kit (Applied Biosystems, Warrington, United Kingdom). Triplicate analysis of blood samples will be conducted and trends of longitudinal increases in mitochondrial DNA levels will be reported.

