#### Muscle oxygenation and Microcirculation

Muscle oxygenation and microcirculatory changes will be measured using the Near Infrared Oxygenation (NIR0) Monitor and the Orthogonal Polarization Spectral (OPS) Microscan respectively.

Muscle (tissue) oxygenation will be measured pre and post intervention daily using the NIRO (NIRO-200, Hamamatsu, Japan) with a probe placed on a peripheral muscle to detect levels of muscle oxygenation (StO_2_) following acute exercise [72]. Muscle oxygen consumption will be further analysed through induced ischemia and active hyperaemia [73]. A pneumatic cuff will be placed above the elbow and inflated to 50 mmHg above the patient's systolic blood pressure and the occlusion will be retained for 3 minutes inducing local ischemia. StO_2 _will be recorded continuously for 3 minutes before, during and after arterial occlusion [44].

Improvements in microcirculation following acute exercise will be measured pre and post intervention session once weekly using the OPS MicroScan (Microvision Medical Inc, Wallingford, PA, USA) with a non-invasive probe placed in the sub-lingual space to detect functional capillary density and blood flow velocity as indicators of microcirculatory function [74] using video images. Five video sequences per patient will be graded by 3 independent observers and assigned a flow velocity score to each of the 4 quadrants of each image [75]. Capillary density will be calculated using superimposed calibrated grid of vertical and horizontal lines on the images of number of small (< 20 μm) vessels crossing the lines of the grid divided by the total length of the lines, yielding the number of small vessels per millimetre [76]. An average of these 5 readings will be calculated for discrete capillary density value for each time point at which imaging was performed.

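### Fat free mass and mitochondrial DNA have no reading at ICU discharge, so patients who leave within about a week have no follow-up value, and carry-forward would score them as zero change

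*Protocol article*

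**What the plan says.** The Muscle Mass section states that fat free mass is "measured at baseline (week 0) and weekly thereafter (till ICU discharge". The Oxidative Stress Markers section states the same for mtDNA: "Mitochondrial DNA (mtDNA) levels in the peripheral blood will be measured at baseline (week 0) and weekly thereafter (till ICU discharge". In both, discharge marks when the weekly series stops, and no reading is attached to it.

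Other outcomes are scheduled differently. Under Primary Outcome Measures, the two physical function tests (ACIF and PFIT) are done at recruitment and at ICU discharge. Under Inflammatory Biomarkers, cytokines are sampled daily in the first week and twice weekly after that.

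The general blood-sampling text under Secondary Outcome Measures describes samples "for the analysis of cytokines, blood lactate and mtDNA levels pre and post intervention during the trial". For mtDNA this does not clearly match a weekly schedule.

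For missing data, the Data Management and Statistical Analysis section says that "if it occurs a carry forward imputation will be done and linear mixed modelling will be used for overall analysis". It plans both intention-to-treat and per-protocol analyses.

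**The concern.** Increased fat free mass and increased mtDNA are named in the secondary hypotheses. Entry requires at least 48 hours of ventilation, which does not ensure a further week in ICU after baseline. A patient discharged on day 6 would contribute a baseline value and nothing else, and one discharged on day 13 would contribute nothing for the last six days.

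The missing value cannot be recovered after discharge, so the analysis has to stand in for it. Carry-forward does this by declaring that the patient did not change. In a disease where the pilot reports loss of fat free mass in controls, that is an implausible value to assign to untreated early leavers, and it erodes the contrast that the trial wants to see.

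**Working it through.** No stated figure is in dispute, so there is nothing in the plan to reproduce. The share of patients with no post-baseline value, q, is not given in the article. It is assumed below and shown over a range.

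**1. Dilution by carry-forward.** If a share q in each arm is assigned zero change, and those patients would otherwise have changed as much as the rest, the expected difference in change becomes d × (1 − q). The Sample size section gives a difference of 0.8 for mtDNA, read here as standardised:

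- q = 10%: 0.8 × 0.9 = 0.72
- q = 30%: 0.8 × 0.7 = 0.56
- q = 50%: 0.8 × 0.5 = 0.40

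These are in units of the original SD. Assigning identical zeros also lowers the observed SD, so the loss of power is smaller than the shrinkage suggests. The estimate itself is still biased towards zero.

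The pilot described under Inflammatory Biomarkers and Exercise gives a figure for fat free mass: a decrease of 7.2% in controls and none with the intervention. If 30% of controls had only a baseline value, 7.2 × 0.7 = 5.0; if 50%, 7.2 × 0.5 = 3.6.

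**2. Loss of information without imputation.** The Sample size section requires 58 per group for mtDNA. At two-sided alpha 0.025 and a standardised difference of 0.8, power with all 58 is 0.98. Using only patients with a follow-up value:

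| Without follow-up | Per group left | Power |
|---|---|---|
| 10% | 52 | 0.97 |
| 30% | 41 | 0.91 |
| 50% | 29 | 0.79 |

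Power is therefore not the main problem unless early discharge is very common.

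**3. Possible selection.** Assume that sicker patients stay longer, that the marker correlates −r with severity, that there is no true effect, and that only patients with a follow-up value are compared. With normal severity, the mean severity of those remaining is m(q) = φ(z_q)/(1 − q), and the bias in SD units is −r × [m(q intervention) − m(q control)]:

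| Left early, control | Left early, intervention | m control | m intervention | Bias, r = 0.3 | Bias, r = 0.5 |
|---|---|---|---|---|---|
| 20% | 20% | 0.350 | 0.350 | 0 | 0 |
| 20% | 30% | 0.350 | 0.497 | −0.04 | −0.07 |
| 20% | 40% | 0.350 | 0.644 | −0.09 | −0.15 |

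A negative sign is against the intervention. The bias needs unequal early discharge and is modest over this range.

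**4. The two mtDNA schedules.** One section says before and after intervention; the other says baseline and weekly. They imply different numbers and times of values, and the article does not say which governs.

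**The case against.** An article condenses its protocol. The words about ICU discharge could have been meant to include a closing reading, and the study diagram is not shown. That is possible, but the same article names a discharge assessment for the physical function tests and none here. If a closing reading is intended, one sentence settles it.

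Three stronger readings are tempting and are not supported.

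- **That microcirculation has the same gap.** It does not: "Improvements in microcirculation following acute exercise will be measured pre and post intervention session once weekly". Each imaged session gives its own pair of values, so a patient imaged in the first week and discharged on day 6 still contributes.
- **That the arms will be compared only among long-stayers.** The statistical section does not restrict the comparison in this way. It plans intention-to-treat, carry-forward and a mixed model. The selection figures above describe a complete-case comparison that the plan does not state.
- **That the trial expects its intervention to shorten ICU stay.** The Background reports that exercise trials in general ICU patients suggest it can "decrease duration of mechanical ventilation, length of hospital and ICU stay and improve overall quality of life". A later section adds that such evidence is not specific to sepsis, and the trial's hypotheses do not mention length of stay. Unequal early discharge is a plausible inference only. Nor does the article support a claim that early leavers would benefit most.

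It is also fair to say that fixed weekly times are a defensible choice, and that replacing them with change from baseline to discharge would create another problem. If the intervention shortened stay and muscle loss builds up over time, intervention patients would show less loss simply because they were measured sooner. That objection stands and shapes the fix.

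Finally, these are secondary outcomes, and mtDNA is called a pilot investigation. Fat free mass is not.

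**Conclusion.** The point holds for fat free mass and mtDNA. On the plain reading, patients who leave ICU within about a week of baseline have no post-baseline value; taking weekly to mean a first reading near day 7 is an interpretation. Carry-forward would then assign them zero change. A difference of 0.8 would fall to about 0.56 with 30% leaving early and to 0.40 with 50%, provided early leavers would have changed as much as the others. Without imputation, the mixed model has no follow-up information on these patients and depends on missing at random.

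Selection bias is a secondary possibility: zero if early discharge is equal in the arms, and up to about 0.15 SD against the intervention under the assumptions shown. The documents cannot fix its size. The primary outcomes are not affected. The change is worth making because it is cheap and because the missing readings cannot be obtained later.

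**What to change.** - **Muscle Mass:** add a final fat free mass reading at ICU discharge, taken with the ACIF and PFIT assessment and subject to the exclusions already listed there (ascites, pleural effusion, renal replacement therapy). Keep the weekly readings.
- **Oxidative Stress Markers:** add an mtDNA value from the buffy coat of the last scheduled blood sample before ICU discharge. Buffy coat is already to be stored, and cytokine sampling already runs until discharge, so no new draw is needed. Keep the weekly values.
- **Secondary Outcome Measures and Oxidative Stress Markers:** reconcile the two statements of mtDNA timing.
- **Data Management and Statistical Analysis:** for these two outcomes, analyse all readings in the planned linear mixed model with actual days since recruitment as time, and do not carry baseline forward. Do not make unadjusted change from baseline to discharge the main contrast, because its timing depends on a post-randomisation event.

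The cost is one extra bioimpedance reading at an existing assessment and one extra PCR run per patient measured for mtDNA. The added values fall on varying days from baseline, which is why actual time has to be modelled. Patients who die in ICU before the first weekly reading will still lack a follow-up fat free mass value.

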### Hypotheses and Aims

The primary research hypothesis of the "i-PERFORM Trial" is that patients with defined sepsis syndromes [57] in the ICU who participate in an early targeted rehabilitation program will have improved physical function and an improved quality of life. The secondary hypotheses is that there will be systemic effects underlying primary improvements which will include; increased fat free mass; decreased pro-inflammatory and increased anti-inflammatory cytokines; increased peripheral blood mitochondrial DNA content and reduced blood lactate levels; and improved tissue oxygenation and microcirculation flow.

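### Fat free mass readings are withheld for conditions that are not entry exclusions, and carrying the last value forward then understates muscle loss

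*Protocol article*

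**What the plan says.** All of the following is in the protocol article.

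- **Muscle Mass.** Fat free mass is read by bioelectrical impedance at baseline and each week until the patient leaves the ICU. The exception is: "If subjects are known to have ascites, a pleural effusion or a renal replacement therapy, measurements will not be done". No substitute measure is given. The readings are to be "analysed to reflect if proteolysis had occurred and resulted in the loss of muscle mass".
- **Inclusion Criteria and the Figure 2 caption.** The exclusions are certain injuries, septic shock that does not respond to treatment, a moribund state and expected death within 48 hours. Ascites, pleural effusion and renal replacement therapy are not among them.
- **Hypotheses and Aims.** "increased fat free mass" is one of the secondary hypotheses, stated for patients with defined sepsis syndromes without restriction.
- **Data Management and Statistical Analysis.** "Mean changes scores, standard deviations and 95% confidence intervals will be calculated". "Analysis will be by both intention-to-treat and per-protocol method". On missing data: "if it occurs a carry forward imputation will be done and linear mixed modelling will be used for overall analysis". There is no exception for readings withheld by rule.

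**The concern.** The measurement rule creates the gaps and the missing-data rule fills them. Together they affect this outcome in two ways.

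First, a patient who has one of the conditions at baseline is randomised but has no baseline reading. There is no change score and nothing to carry forward. That patient drops out of an analysis described as intention-to-treat, while the hypothesis is stated for all patients with sepsis.

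Second, a patient who develops a condition later stops being measured for as long as it lasts. Carry-forward freezes the score at the last reading. The expected course is downward: the Background says that sepsis can speed up muscle wasting, and the pilot found a loss in controls. Freezing a falling measure understates the loss.

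The reason for the gap is plausibly related to illness, and each condition can begin after randomisation. If the arms differ in how often readings are withheld, carry-forward alone can shrink a real difference or create a false one.

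**Working it through.** The article gives no figure for this point that could be reproduced, and no rate for the three conditions. The check is a reading of the two rules together, followed by illustrative arithmetic.

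**Inputs**
- Size of loss: 7.2 in the pilot's control arm and no decrease in its intervention arm (Inflammatory Biomarkers and Exercise). It is treated here as points of percentage fat free mass.
- Schedule: baseline, then weekly (Muscle Mass).
- Share p of patients with readings withheld after baseline: not given; 10% to 40% assumed.

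**Step 1: what carry-forward records for one patient.** Assume a linear loss of 7.2 points over W weeks, with the condition starting before the week k reading and lasting to ICU discharge. The last reading is then at week k − 1, and the recorded loss is 7.2 × (k − 1) / W.
- W = 3: onset before week 1, 2 or 3 records 0, 2.4 or 4.8.
- W = 4: onset before week 1, 2, 3 or 4 records 0, 1.8, 3.6 or 5.4.

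The recorded loss is always below 7.2, but it is zero only when onset precedes the week 1 reading.

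**Step 2: dilution of a true difference.** Suppose controls lose 7.2, intervention patients lose nothing, and a share p is affected in both arms. Carry-forward leaves the intervention arm at zero, so the recorded difference is the recorded control loss.

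| p | Baseline carried: 7.2 × (1 − p) | Half the loss already recorded: 7.2 × (1 − p) + 3.6 × p |
|---|---|---|
| 10% | 6.48 | 6.84 |
| 20% | 5.76 | 6.48 |
| 30% | 5.04 | 6.12 |
| 40% | 4.32 | 5.76 |

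**Step 3: a false difference when there is none.** Suppose both arms truly lose 7.2, with readings withheld in 40% of one arm and 20% of the other.
- Baseline carried: 7.2 × 0.6 = 4.32 against 7.2 × 0.8 = 5.76, a false difference of 1.44 points.
- Half the loss already recorded: 5.76 against 6.48 (from the table), a false difference of 0.72 points.

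The arm with more withheld readings appears to lose less, so the error favours that arm. If that arm is control, the error runs against rehabilitation; if it is intervention, the error runs in its favour.

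**Step 4: the mixed model.** A linear mixed model fitted to observed readings would not score affected patients as unchanged. Fitted after carry-forward, it would inherit the errors in steps 1 to 3. The sentence names both methods and does not say how they fit together.

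**The case against.** The strongest reply has five parts.

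- **Withholding the reading is defensible.** The section already controls for fluid by estimating fluid balance and emptying catheters, and the three conditions could distort impedance. This stands. The weakness lies in how the gaps are handled, and nobody should be asked to take invalid readings.
- **Carry-forward is not the only method named.** A reader who stops at the imputation clause might infer that it alone governs the analysis. The same sentence names linear mixed modelling. This stands as far as it goes: the text leaves open which values the model uses. It still states that carry-forward is to be done.
- **Loss already recorded is kept.** A reader might infer that everyone affected after baseline is scored as having lost no muscle. The weekly schedule does not support that, as step 1 shows. Nor is withholding permanent: a patient whose condition resolves can be measured again at the next weekly reading.
- **The link to severity is an inference.** A reader might say that the sickest patients go unmeasured. The article does not say so, does not link these conditions to greater wasting and gives no frequency for them. A relation to illness is plausible, and that is all the point requires.
- **An article leaves detail to the full protocol or analysis plan.** An outcome-specific analysis set or a sensitivity analysis may be set out there. That is fair, and their absence is not the finding. The finding is that two rules which the article does state combine badly for this outcome.

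**Conclusion.** The point holds for the handling of the gaps and for the reach of the conclusion. Patients affected at baseline have no change score. Patients affected later are credited with no further loss after their last reading wherever carry-forward is applied. This understates loss in a declining measure and can bias the comparison in either direction.

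The size depends on rates that the article does not give. With 10-40% affected in both arms, a true 7.2-point difference falls to between 6.5 and 4.3 if baseline is carried for all affected patients, which is the upper limit of the dilution, or to between 6.8 and 5.8 if half the loss was already recorded. A 40% against 20% imbalance creates a false difference of up to 1.4 points. It would be wrong to read that figure as a bias towards rehabilitation, because its sign depends on which arm has more withheld readings, and the article gives no ground for expecting either.

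Fat free mass is a secondary, mechanistic outcome. The primary conclusions and the main sample size do not depend on it. The change should be made, but it does not threaten the trial.

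**What to change.** For fat free mass:

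1. Do not carry values forward. Fit the linear mixed model already named to the observed readings, adjusting for the baseline SOFA and APACHE II scores already collected (Demographics).
2. Add one sensitivity analysis that assigns withheld readings the control-arm mean loss or worse.
3. Report the number of withheld readings by arm and by reason.
4. Limit the conclusion to patients who could be measured at baseline.

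The measurement rule itself can stay as it is. The cost is a change of analysis wording and a tally of reasons. Precision is slightly lower than with filled-in values, and the conclusion covers a narrower population. The baseline scores account only partly for illness that arises after baseline, so the model on observed readings does not remove all the bias. The sensitivity analysis is needed for that reason.
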